### Plan for statistical analysis

Data will be presented using descriptive statistics: mean values (SD) for normally distributed data, median (range/min, max) for data that are not normally distributed, and counts with percentages for categorical data.

The main comparison between digital assessment and clinical evaluation for each timepoint will be done with McNemar test (binary categorization) or Bowker test (more than two categories) for disagreement. Digital assessment will be categorized with different thresholds or a traffic light model (“child is developing typically”, “a possible risk or a clear risk”) and clinical assessment will be categorized to categories: “no concern”, “concerns requiring clinical intervention including specialist consultations, further investigations, additional controls/follow-up visits, prescription medication or supplements or referral for treatment or therapy”. Also, agreement and it’s 95% confidence interval will be calculated. Furthermore, sensitivity, specificity, positive and negative predictive values will be calculated (compared to clinical assessment).

Pearson’s or Spearman’s correlation coefficients will be generated to evaluate the linear relation between continuous variables.

In addition, to study the association between predictor and response variables within ePipari or clinical assessment visits, linear models or logistic regression models can be built up. The effect of confounding factors (such as socio-economic status, pregnancy week when child was born) will be taken into account, as appropriate. For those measurements which are evaluate repeatable, linear mixed models suitable for repeated measurements will be used.

Statistical analyses will be performed using SPSS version 29 or later or SAS System, version 9.4 for Windows or later. Two-sided p-value < 0.05 will be considered as statistically significant. Confidence intervals of 95% will be calculated, especially for feasibility part of the study.

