## Methods

### Aims

The aim of this prospective study is to investigate whether the ePIPARI is a feasible and valid tool for follow-up of preterm infants in identifying children and families in need of further clinical interventions or support compared to clinical follow-up. We hypothesize that 1) ePIPARI is a feasible tool for the follow-up of preterm infants and their parents, and 2) it is comparable to routine clinical follow-up in recognizing children and parents in need for requiring interventions.

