### The evaluation of feasibility and performance

The evaluation of feasibility is based on the knowledge of how parents have taken part in the study and how they have completed the questionnaires of ePIPARI at different age points. Furthermore, the anonymous survey of user-experience provides descriptive information on how parents have experienced the questionnaire, the technical usability of the ePIPARI, and its content.

The validity of the ePIPARI is evaluated based on its ability to identify children and parents in need of further support and clinical interventions in comparison to clinical visits. The outcomes to be compared are: concerns requiring clinical intervention including specialist consultations, further investigations, additional controls/follow-up visits, prescription medication or supplements or referral for treatment or therapy.

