### Sample size and statistical power

Approximately 50–60 very preterm infants enter the clinical follow-up at Turku University Hospital every year and 600–650 children born prematurely are examined in the Preterm Infant Follow-up Clinic each year. Power calculations were performed to detect the children needing interventions or further follow up at 2 years of corrected age. Using data collected from ePIPARI for this age-point, we get the minimum sample size 26 participants, to achieve a power of 80% and a two-sided significance of 5% for detecting a difference of 35% between web-based and clinical evaluation (42% vs 77%) for further follow-up need. While both evaluations are made for all children, also moderate association between evaluations was assumed (correlation between paired observations was assumed to be 0.35) [Reference: Dhand, N. K., & Khatkar, M. S. (2014). Statulator: An online statistical calculator. Sample Size Calculator for Comparing Two Paired Proportions. Accessed 25 April 2023 at http://statulator.com/SampleSize/ss2PP.html]. The estimated data collection time to achieve the predetermined number of participants is 2–3 years, as not all the families agree to participate in the ePIPARI Study. The data collection is ongoing, and the analysis will start when data has been accumulated.

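### The main test and the power basis address a difference in referral rates, while hypothesis 2 is that ePIPARI is comparable to the clinic in recognising those in need

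*Protocol article*

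**What the plan says.** All references are to the Methods of the protocol article.

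- **Aims**, hypothesis 2: "it is comparable to routine clinical follow-up in recognizing children and parents in need for requiring interventions".
- **The evaluation of feasibility and performance**: "The validity of the ePIPARI is evaluated based on its ability to identify children and parents in need of further support and clinical interventions", with clinical visits as the comparison.
- **Sample size and statistical power**: a minimum of 26 participants at 2 years of corrected age, at 80% power and a two-sided 5% level, "for detecting a difference of 35% between web-based and clinical evaluation (42% vs 77%) for further follow-up need". The correlation between paired observations is assumed to be 0.35.
- **Plan for statistical analysis**: "The main comparison between digital assessment and clinical evaluation for each timepoint will be done with McNemar test (binary categorization) or Bowker test". The test is described as one for disagreement, and two-sided p < 0.05 counts as significant. The same section adds agreement with a 95% confidence interval, and then: "sensitivity, specificity, positive and negative predictive values will be calculated (compared to clinical assessment").
- The categories listed there are two for the clinical assessment (no concern, or concerns requiring intervention). The example for the digital assessment also has two, with possible and clear risk taken together.

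**The concern.** The aim is to show that two assessments recognise the same children and families. McNemar's null hypothesis is that the two marginal percentages are equal. Rejecting it shows that one method flags more children than the other. Not rejecting it shows only that no such imbalance was detected. Neither outcome says whether the children flagged by ePIPARI are the ones the clinic found to be in need. The sample size follows the same logic: it is set to detect a 35-point difference in rates, not to exclude a difference or to estimate accuracy.

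The tool is meant to let well children skip routine visits without loss of safety (Discussion), so the costly error is the missed child. The main test does not isolate that error. It sets missed children against extra referrals and looks only at the balance.

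**Working it through.** **Inputs.** From the sample size section: p1 = 0.42, p2 = 0.77, correlation ρ = 0.35, two-sided α = 0.05, power 80%, n = 26.

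**Step 1. Reproduce the plan's figure.**

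- Both positive: p11 = p1·p2 + ρ·√(p1q1p2q2) = 0.396.
- Discordant cells: 0.420 − 0.396 = 0.024 and 0.770 − 0.396 = 0.374.
- Both negative: 0.206.
- Total discordance ψ = 0.398; difference δ = 0.35.
- (1.960 + 0.842)²·ψ/δ² = 25.5, rounded up to 26. The Connor formula gives 22.98, and 25.76 with continuity correction, also rounded up to 26.

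The stated 26 is reproduced. Exact McNemar power at n = 26 is 83.7%. The arithmetic is sound for a test of difference.

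**Step 2. What the planning values imply for accuracy.** The two-sided McNemar p-value depends only on the two discordant counts and is unchanged when they are swapped. The accuracy is not unchanged:

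| Which rate is ePIPARI's | Sensitivity | Specificity |
|---|---|---|
| 42% (clinic 77%) | 0.396/0.77 = 51% | 0.206/0.23 = 90% |
| 77% (clinic 42%) | 0.396/0.42 = 94% | 0.206/0.58 = 36% |

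A tool that misses about half of those in need and one that misses about 6% therefore get the same main result.

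**Step 3. A tool with no discrimination.** Let ePIPARI flag 42% at random while the clinic flags 42%. Then sensitivity is 42%, specificity 58%, and agreement 0.42² + 0.58² = 51%. Share of studies with p > 0.05, by enumeration over the discordant pairs:

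| n | Asymptotic | Exact |
|---|---|---|
| 26 | 95.6% | 97.5% |
| 150 | 94.9% | 96.2% |

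The null hypothesis is true here, so a 5% test must behave this way. A larger sample cannot change it.

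**Step 4. A tool that misses no child.** Take sensitivity 100%, specificity 70% and a clinic rate of 42% (assumed values). The discordant cells are 0.58 × 0.30 = 0.174 and 0. McNemar rejects in 69% of studies (asymptotic) or 29% (exact) at n = 26, and in about 100% at n = 100.

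**Step 5. Power for smaller gaps in rates.** ρ = 0.35; each range covers a gap measured up from 42% or down from 77%:

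| n | True gap | Exact | Asymptotic |
|---|---|---|---|
| 26 | 20 points | 29–31% | 39–44% |
| 26 | 25 points | 46–49% | 58–62% |
| 60 (assumed) | 20 points | 71–77% | 79–83% |

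At n = 26, a true 20-point gap would thus be non-significant in 56–71% of studies, depending on the test version and the base rate.

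**The case against.** Four points on the other side deserve weight.

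1. **No pass rule is stated.** A reader might infer that p > 0.05 will be taken as support for hypothesis 2, so that a useless tool would pass. The article does not say so; it only defines p < 0.05 as significant. That reading is not supported, and the point here does not need it: the test does not address the hypothesis in either direction.
2. **The informative measures are planned.** Agreement with its interval, sensitivity, specificity and predictive values are all in the same section. The random tool of Step 3 would show agreement near 51% and would not go unnoticed. This stands and limits the severity. What remains is that these measures follow the main comparison and did not determine the sample size. The absence of success values from the article is not itself a fault, since an analysis plan not shown here may hold them.
3. **26 is a minimum.** With 50–60 very preterm infants a year and 2–3 years of collection, the achieved number could be larger. Step 5 shows that this eases the power problem. It does nothing for Steps 2 and 3.
4. **Referral rates matter too.** The study also aims at fewer unnecessary visits, so over- or under-referral is worth reporting. That justifies keeping McNemar as a description, not as the main answer.

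A reader might also infer that the Bowker option makes the analysis unworkable. It does not. It is offered only for more than two categories, and the categories listed run as a two-by-two McNemar table. This is a matter of wording.

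**Conclusion.** The mismatch is real. Hypothesis 2 and the definition of validity concern recognising those in need; the main comparison and the power basis concern a difference in marginal rates. Steps 2 and 3 hold whatever the sample size: under the plan's own values the test cannot tell sensitivity of 51% from 94%, and a tool with no discrimination at an equal flagging rate is non-significant in about 95–98% of studies. The low power for a 20-point gap applies at the stated minimum of 26 and assumes the planned correlation of 0.35; it means that at this size non-significance would not show comparability even of the rates.

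The conclusion does not extend to the sample size arithmetic, which is reproduced, or to a claim that the study will miss a poor tool, because the planned accuracy measures would reveal one.

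**What to change.** - **Main analysis:** sensitivity and specificity of ePIPARI against the clinical assessment at 24 months, the age used for the power calculation, with exact or Wilson 95% confidence intervals.
- **Criterion:** judge comparability by the lower confidence limits against minimum values that the investigators fix in writing before the two data sets are linked.
- **McNemar:** keep it as a secondary description of over- or under-referral, with the paired difference and its 95% confidence interval, and state that p > 0.05 is not evidence of comparability.
- **Bowker:** use it only where both assessments have the same three or more categories. As listed, the clinical assessment has two.

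**Cost.** The change is to the wording of the analysis and needs no new data. Precision is the price. At n = 26, about 11 (0.42 × 26) to 20 (0.77 × 26) children would be clinic-positive. As examples, 9 of 11 identified gives an exact 95% interval of 48–98%, and 18 of 20 gives 68–99%. Near the minimum size the result may be inconclusive and the claim less favourable, and the intervals should be reported as such. As an assumed illustration, showing sensitivity above 70% when the truth is 90% takes 31 clinic-positive children (exact test, one-sided 2.5%, power 80%), and 61 when the truth is 85%.

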#### Family well-being

*Parental sleep quality* is evaluated at each age point, but a more detailed questionnaire is sent to both parents when the child is at 8 months of corrected age. The quality of parents’ sleep at 8 months of corrected age is assessed using 8 items extracted from the original Basic Nordic Sleep Questionnaire (BNSQ) [32, 33]. The *family`s well-being* is examined by asking about the social support they have received as regards formal or/and informal support, and the help they would like to have to give them more support with everyday life. *Parental depressive symptoms* are assessed separately from both parents when the child is at 8 months and 12 months of corrected age by *the Edinburg Postnatal Depression Scale* [34] which has been widely used to assess maternal depression. A cut-off value of 13 is used. In addition, *marital satisfaction* is assessed with The Revised Dyadic Adjustment Scale, RDAS [35] when the child is at 8 months of corrected age. The RDAS is a shortened version of the Dyadic Adjustment Scale [36]. It consists of 14 items designed to measure adjustment in dyadic relationships on 3 sub-scales: Consensus, Satisfaction and Cohesion.

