### Participants and recruitment procedure

The recruitment process is ongoing. Parents of all preterm children, who meet the inclusion criteria during 4/2019–12/2022 are approached before discharge and asked to participate in the “ePIPARI—web-based follow-up of preterm infants”. The inclusion criteria for the infants and the parents are 1) infant is born before 34 gestational weeks, 2) infants have systematic developmental follow-up in pediatric unit in Turku University Hospital and 3) parents speak Finnish, Swedish or English. Inclusion criteria for participating only in the two-year corrected age was that the child is born before 32 gestational weeks during 2019–2021. We excluded infants, who didn’t have clinical follow-up in Turku University Hospital and parents, who couldn`t speak Finnish, Swedish or English.

Recruitment takes place in the neonatal intensive care unit by a registered nurse or a PhD-student ([name]) and the link for registration is sent to the parents’ email. After registration, parents log into ePIPARI via email or via a Mobile App by using a secure strong recognition. Advice and support for logging in is provided by a nurse before discharge. All preterm born children have the routine follow-ups regardless of their participation in the study.

The ongoing data collecting process is as follows: A digital invitation to complete the age-point specific questionnaires is sent two weeks prior to each age-point to parents’ email or to Mobile App. Parents can complete the questionnaires together or only by another, but queries related to family well-being are sent to both parents separately (Table 1). Reminders are sent if the questionnaires are not filled in. The aim is for the questionnaires to be completed before the clinical follow-up visits and so that afterwards the answers can be compared to the (written) medical records made in the clinical visits. The staff of the Pediatric unit will be blinded for the data of the ePIPARI so that it does not affect their assessment during clinical visits. Experienced medical doctors evaluate the answers of the questionnaires at two weeks intervals and estimate the amount of concern based on the responses and pre-set cut-off points. If there is significant concern that was not evident during the clinical follow-up visit, the medical doctor contacts the family or staff of the neonatal follow-up clinic.

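### The main comparison uses methods that assume independent children, while eligibility admits siblings from multiple births; if siblings are analysed, intervals will be somewhat too narrow

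*Protocol article*

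**What the plan says.** All places are in the Methods of the protocol article.

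- **Plan for statistical analysis.** The digital and clinical assessments are compared at each age point by McNemar's test (two categories) or Bowker's test (more than two). In addition, "agreement and it’s 95% confidence interval will be calculated", and sensitivity, specificity and predictive values are estimated against the clinical assessment. No family cluster, sibling rule or robust variance is named. The one provision for correlated records concerns measurements repeated over time, for which "linear mixed models suitable for repeated measurements will be used".
- **Sample size and statistical power.** The calculation is for the 24-month comparison: "we get the minimum sample size 26 participants". The only dependence allowed for is that between the two evaluations of the same child: "correlation between paired observations was assumed to be 0.35".
- **Participants and recruitment procedure.** Parents of every eligible child born before 34 weeks are approached. Multiple births are neither excluded nor mentioned.
- **Parental scales.** Under Family well-being, depressive symptoms are "assessed separately from both parents when the child is at 8 months and 12 months of corrected age". The recruitment section adds that "queries related to family well-being are sent to both parents separately". Footnote a of Table 1 also marks behaviour and social relationships at 18 months as answered by each parent. Nothing says how two parents' records enter the analysis.

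**The concern.** Families are approached, but children are compared. Where a family has two or three eligible infants, the same parents fill in each child's questionnaires and the same clinic examines each child. How a parent reports is part of what drives the discrepancy between the digital and the clinical assessment, so that discrepancy can plausibly be alike in siblings. Two siblings then carry less information than two unrelated children, and a standard McNemar test or binomial interval counts them in full.

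What is at stake is the stated precision. The Discussion wants to reduce routine visits without loss of safety. That rests mainly on sensitivity and negative predictive value, and on how far below the estimate their lower limits lie. The plan deals with dependence within a child and over time, but not within a family.

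**Working it through.** **1. The plan's own figure.** Inputs from Sample size and statistical power: proportions 0.42 and 0.77, correlation 0.35, two-sided 5%, power 80%.

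- Covariance = 0.35 × √(0.42 × 0.58 × 0.77 × 0.23) = 0.0727.
- Both positive: 0.42 × 0.77 + 0.0727 = 0.396.
- Discordant cells: 0.42 − 0.396 = 0.024 and 0.77 − 0.396 = 0.374; sum pd = 0.398; difference d = 0.35.
- Usual unconditional McNemar formula, [1.960√pd + 0.842√(pd − d²)]² / d² = 22.98, so 23.
- The same with a continuity correction: 25.76, so 26.
- Null-variance form, (1.960 + 0.842)² × pd / d² = 25.49, so 26.

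The stated 26 is reproduced by two standard variants. All three treat the children as independent, that is, with a design effect of 1.

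**2. Design effect from siblings.** The documents give neither input, so both are assumptions:

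- f, the share of infants in twin pairs: 0.2–0.4;
- ICC, the intra-family correlation of the quantity analysed (the paired difference for McNemar, the agreement indicator for the agreement interval): 0.3–0.7.

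With clusters of one or two, the design effect is DE = 1 + f × ICC. The true standard error is √DE times the naive one, and the naive one is too small by 1 − 1/√DE. The actual type I error of a nominal 5% test is 2 × [1 − Φ(1.960/√DE)], and the actual coverage of a nominal 95% interval is 1 minus that.

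| f | ICC | DE | True SE ÷ naive SE | Naive SE too small by | Actual type I error | Actual coverage |
|---|---|---|---|---|---|---|
| 0.2 | 0.3 | 1.06 | 1.030 | 2.9% | 5.7% | 94.3% |
| 0.3 | 0.5 | 1.15 | 1.072 | 6.7% | 6.8% | 93.2% |
| 0.4 | 0.7 | 1.28 | 1.131 | 11.6% | 8.3% | 91.7% |

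**3. Effect on the minimum of 26.** Multiplying by DE: 26 × 1.06 = 27.6, so 28; 26 × 1.15 = 29.9, so 30; 26 × 1.28 = 33.3, so 34. By the uncorrected formula, power at 26 children is 85% with independence. With an effective number of 26/1.06 = 24.5 it is 83%, and with 26/1.28 = 20.3 it is 74%.

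These are large-sample approximations, and at 26 children they show the order of magnitude only.

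**The case against.** The strongest objection is that this reads a fault into silence. The article never says that records are treated as independent, twins are not mentioned, and a condensed article may leave sibling handling to a fuller plan. In part this stands: the conclusion has to be conditional on siblings being analysed and on positive correlation. It does not remove the point. The article does fix the main test, eligibility as written lets siblings in, and the standard form of that test does not fit such a sample.

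A second objection is size. The true standard error is at most about 13% larger under the assumed ranges, against a planned difference of 35 points, and 26 is called a minimum. This stands for the test at 24 months. It has less force for the accuracy measures, where the interval is the result. There too the effect may be smaller than tabulated: sensitivity and specificity cluster only through sibling pairs with the same clinical status, so the effective share in pairs is lower.

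Three stronger readings are tempting, and the documents do not support them:

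- *The parental results are the worst affected, because mothers and fathers are pooled or a twin family's score enters once per child.* The article says only that parents answer separately. It describes neither pooling nor duplication, and a separate analysis of each parent would remove the issue.
- *The plan applies a linear mixed model to the binary concern outcome.* It assigns mixed models to repeatedly evaluated measurements, makes the binary comparison at each age point, and offers logistic regression among the association models.
- *The sample size of 26 is wrong.* It reproduces on its own inputs; it merely has no allowance for families.

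**Conclusion.** The point holds in conditional form. The named methods assume independent children, and eligibility as written admits siblings. If siblings are analysed without adjustment, and their agreement or paired-difference indicators are positively correlated, the intervals will be too narrow and the McNemar type I error above 5%. With 20–40% of infants in twin pairs and an ICC of 0.3–0.7, the design effect is 1.06–1.28: the true standard error is about 3–13% larger than the naive one or, put the other way, the naive one is about 3–12% too small. Both ranges are assumptions. Triplets would add to the effect, and a low correlation of the paired difference would make it negligible. The effect is small to moderate, but it can be avoided. For the parental scales there is no demonstrated error, only a rule worth stating.

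**What to change.** Name the family as the cluster in the analysis plan.

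- **Paired difference:** a cluster-adjusted McNemar test, or GEE with family-robust standard errors.
- **Agreement, sensitivity, specificity and predictive values:** a family-level bootstrap or family-robust standard errors. An analysis with one child per family can serve as a sensitivity check.
- **Parental scales:** count each parent once, and analyse the two parents separately or with family-clustered standard errors. This is a safeguard, since the plan does not say that it pools them.
- **Reporting:** give the number of families and of multiples beside the number of children.

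The cost is slightly wider intervals and a little more programming. A family identifier is needed in the analysis file; the article does not say whether one is held. The article describes data collection as ongoing and the analysis as not yet started, so the change can still be made in advance.

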### The structure of ePIPARI

ePIPARI is a digital follow-up tool on a web-based platform. It provides comprehensive follow-up for preterm children and their parents from term age until 2 years of corrected age. ePIPARI-follow-up tool was developed by the multidisciplinary PIPARI Study group and the staff of the Pediatric Unit of Turku University Hospital and is based on international recommendations and relevant literature. In addition, clinical knowledge and expertise gained from the PIPARI-study have been utilized in the development of the tool. The PIPARI Study group consist of researchers and experts from different disciplines, including pediatric and adolescent medicine, nursing science, pediatric neurology, psychology, neuropsychology, speech-language pathology, public health, psychiatry, physiotherapy and neuroradiology. The content and questionnaires of each time point in ePIPARI were developed and planned in collaboration with this multidisciplinary team. The permission to use standardized assessments and copyright-related issues has been taken into account. In addition, the nurses of Preterm Infant Follow-Up Clinic and Neonatal Intensive Care of Unit participated in planning the content. The technical implementation of the web-based material was carried out by Kaiku Health-company, whose web-based platform was already in use at Turku University Hospital in Pediatric Oncology Unit.

ePIPARI includes eight assessment points: term age, 1, 2, 4, 8, 12, 18 and 24 months of corrected age. It evaluates the child´s health and growth, eating and feeding, neurodevelopment (development of motor skills, language, cognition, behavior, and socials skills) and family wellbeing (parental depression and marital satisfaction) (Table 1). Responses are classified for typical development, growth and behavior or responses of concern using different thresholds or a traffic light model. Widely used standardized questionnaires, and age-appropriate clinical questions are used (Table 2). ePIPARI also provides videos of health and typical development, as well as written information on how to support a child’s development and how to get help with concerns related to parenting or child’s developmental problems.

**Table 1 Tab1:** ePIPARI – Web-based follow-up of preterm infants. Age points (corrected age) and topics

	Term age	1 month	2 months	4 months	8 months	12 months	18 months	24 months
Health	x	x	x	x	x	x	x	x
Growth	x	x	x	x	x	x	x	x
Feeding and eating	x	x	x	x	x	x	x	x

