#### Neurodevelopment

*Motor development* is outlined with questions related to age-appropriate motor development at each age point beginning from 2 months of corrected age. Parents are asked for example if the child is able to maintain her/his head upright, whether the child uses both hands and legs equally, and what kind of postures and motility is typical for the child. The tutorial videos on ePIPARI are offered to help parents to answer the questions about motor skills. If there is any deviation from the expected age-appropriate level, additional detailed follow-up questions then follow. Concerns about motor development are evaluated using a traffic light model for each item, where green indicates that child is developing typically, yellow means a possible risk, and red a clear risk of developmental problems.

Information on the emerging *language and communication ability* is collected at 12 and at 24 months of corrected age using the Finnish short form versions of MacArthur Communicative Development Inventories, FinCDI-SF [23–25] and different composites of the Finnish version of the Infant–Toddler Checklist of the Communication and Symbolic Behavior Scales Development Profile (FinCSBS-ITC) [26, 27]. Both methods have been adjusted using norming and validated for the Finnish population, and they provide information on early receptive and expressive lexical development and early communicative behavior (i.e. expression of emotions, use of gaze, communication ability, gesture, and object use). The cut-off points of the norming population for these methods (the weakest 10^th^ percentile) are used to identify children at risk for language development and communication.

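### In the secondary association models, every repeated measurement is assigned to a linear mixed model, although some repeated responses are categorical (minor)

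*Protocol article*

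**What the plan says.** All of the following is in the Protocol article.

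- **Main comparison** (Plan for statistical analysis): "The main comparison between digital assessment and clinical evaluation for each timepoint will be done with McNemar test (binary categorization) or Bowker test" when there are more than two categories. Agreement, sensitivity, specificity and predictive values accompany it.
- **Association models** (same section, later paragraph): "linear models or logistic regression models can be built up" for predictors and responses within the web tool or within the clinic visits, with adjustment for confounders as appropriate. The paragraph closes with the rule at issue: "For those measurements which are evaluate repeatable, linear mixed models suitable for repeated measurements will be used". No generalized mixed model, GEE or ordinal model is named anywhere.
- **Number of occasions** (The structure of ePIPARI): "ePIPARI includes eight assessment points: term age, 1, 2, 4, 8, 12, 18 and 24 months of corrected age".
- **Categorical responses that recur.** Table 1 lists health and feeding at all eight ages, and the Health and growth section grades clinical problems by category of concern. For motor skills, from 2 months on (six ages in Table 1), the Neurodevelopment section says "Concerns about motor development are evaluated using a traffic light model for each item". That scale has three ordered colours, running from typical development through possible to clear risk. The validity outcome is itself a yes/no concern: "The outcomes to be compared are: concerns requiring clinical intervention including specialist consultations", followed by further kinds of intervention.
- **Continuous responses that recur.** Weight, length and head circumference are requested at every age (Health and growth). The Edinburgh depression score is collected from both parents at 8 and 12 months (Family well-being).

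**The concern.** For responses measured once, the paragraph offers a linear or a logistic model, so the type of response is recognised there. For responses measured repeatedly it names one model, the linear one, and says that it will be used. Read literally, a yes/no concern recorded at up to eight ages would be fitted on a straight-line risk scale with normal errors.

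A binary response has variance p(1−p), which changes with the risk, and its mean must lie between 0 and 1. A linear mixed model imposes neither property. When concerns are uncommon, the standard errors of age trends and risk-factor effects can be too small, and some children can receive fitted risks below zero. What is at stake is the reliability of secondary results on, for example, gestational age or socio-economic status as predictors of recurrent concerns.

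**Working it through.** **1. The plan's own figure.** Inputs from Sample size and statistical power: 42% and 77%, correlation 0.35, 80% power, two-sided 5%.

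- Both positive: 0.42 × 0.77 + 0.35 × √(0.42 × 0.58 × 0.77 × 0.23) = 0.3234 + 0.0727 = 0.3961.
- Discordant cells: 0.42 − 0.3961 = 0.0239 and 0.77 − 0.3961 = 0.3739; sum 0.3978.
- N = (1.96 + 0.8416)² × 0.3978 / 0.35² = 25.5, rounded up to **26**.

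The stated 26 is reproduced. The McNemar formula with separate null and alternative variances gives 23.0, and 25.8 (also 26) with continuity correction. No mixed model enters any of these, so the sample size does not depend on this point.

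**2. Where each response goes.**

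| Response | Ages | Main comparison | If modelled as repeated |
|---|---|---|---|
| Weight, length, head circumference | 8 | – | linear mixed: suitable |
| Depression score, total | 2 | – | linear mixed: suitable |
| Health and feeding categories | 8 | McNemar or Bowker per age | linear mixed as written: not suitable |
| Motor traffic light | 6 | McNemar or Bowker per age | linear mixed as written: not suitable |

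**3. Size of the effect, by simulation.** Prevalence, effect sizes and number of children are assumptions, because the article gives none for this purpose. Binary data at the eight ages (time t = months/24) came from a logistic model with intercept b0, time slope b1, a standard normal child-level covariate with slope b2, and a normal child effect with SD 1. Each data set was analysed with a random-intercept linear model. For complete data this has a closed form, with g the centred covariate:

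- Time slope: Σ(y_ij − ȳ_i)(t_j − t̄) / [nΣ(t_j − t̄)²], with SE = √{s²_within / [nΣ(t_j − t̄)²]}.
- Covariate slope: Σȳ_i g_i / Σg_i², with SE = √(s²_between / Σg_i²).

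There were 4,000 data sets per row. Coverage is that of estimate ± 1.96 SE for the average estimate, so it tests the standard error alone. Paired entries are time / covariate.

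| n; b0, b1, b2 | Prevalence | Mean SE / true SD | Coverage | Outside 0–1, fixed part | Outside 0–1, with child effects |
|---|---|---|---|---|---|
| 60; −0.3, 0.8, −0.5 | 49.6% | 1.00 / 1.05 | 95.1% / 95.4% | 0.0% | 0.2% |
| 120; −0.3, 0.8, −0.5 | 49.7% | 1.00 / 1.05 | 94.8% / 95.9% | 0.0% | 0.1% |
| 120; −2.5, 1, −0.7 | 15.8% | 0.93 / 0.93 | 93.6% / 92.6% | 3.4% | 5.0% |
| 120; −3.2, 1, −0.8 | 9.7% | 0.90 / 0.84 | 91.4% / 89.6% | 6.9% | 8.6% |
| 120; −4, 3, −0.8 | 11.3% | 0.76 / 0.90 | 86.3% / 91.9% | 14.9% | 20.0% |

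Near 50% nothing material happens. Near 10%, standard errors are 10 to 16% too small, and 24% too small for time when the trend is steep.

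**4. Which row applies?** The only rates in the article are 42% and 77%, at 24 months. By symmetry 77% behaves like 23%, between the first and third prevalence levels of the table, so neither rate is in the rare range. The article gives no rates for other ages. One anchor is that the language cut-offs mark the lowest tenth of the norming population at 12 and 24 months, but that is not a rate for this preterm cohort.

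**The case against.** The strongest reply is that the sentence was meant for growth and questionnaire scores, which do recur and which a linear mixed model fits well. It closes a paragraph on optional extra analyses, the same paragraph mentions logistic regression, and a condensed article may leave the link function and covariance structure to an analysis plan that is not shown.

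Much of this stands. The analyses are secondary, part of the repeated data is continuous, and the intention may well have been narrower than the wording. What does not stand is the appeal to an unseen plan. The article does not leave the choice open: it states which model will be used and sets no limit on the type of response. An analysis plan would have to follow that rule or contradict it.

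Stronger readings are tempting, and the documents do not support them:

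- A reader might infer that the digital-versus-clinical comparison is analysed with the wrong model. It is not; it is tested separately at each timepoint.
- A reader might infer that intervals for age-specific concern rates will be distorted by one common residual variance. No section says that a mixed model will estimate those rates, and no covariance structure is fixed. The simulation assumes a common variance. Visit-specific variances would deal with differences between ages, though not with differences between children at low and high risk, nor with fitted risks outside 0 to 1.
- A reader might infer that these models settle which families need more visits. The Discussion gives individualised follow-up as the purpose of the project but does not tie it to them.
- A reader might take the traffic light to be analysed at three levels. It is collected that way, but the analysis section prints two categories: "a traffic light model (“child is developing typically”, “a possible risk or a clear risk". The Bowker test is available for more than two, so the analysed form is unsettled.

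**Conclusion.** The point holds as a minor one. The rule for repeated measurements is worded too broadly: it sends repeated categorical responses to a linear mixed model, and no suitable model is named for them.

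The harm is conditional. At an assumed concern rate near 10%, coverage falls to about 86 to 92% and 7 to 20% of fitted risks lie outside 0 to 1. At about 16% the loss is small (coverage about 93 to 94%), and near 50% it is negligible. These figures rest on assumed prevalences, effects, 60 or 120 children with complete visits, and a random intercept with one residual variance. They show what can happen, not what will happen in this cohort.

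**What to change.** Replace the sentence with wording such as:

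> Repeated continuous measurements (growth measures, total depression score) will be analysed with linear mixed models. Repeated binary responses will be analysed with logistic GEE or a logistic mixed model. Ordered categories, if kept at three levels, will be analysed with a cumulative-logit mixed model; if a category is sparse, yellow and red will be merged and the binary model used.

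State also whether the traffic light is analysed at two or three levels, so that it is clear which clause applies.

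The cost is a few lines of text. SPSS and SAS, both already named, fit these models, and the article says that analysis starts only once data have accumulated, so the change can be made beforehand. The practical price is that a cumulative-logit mixed model may fail to converge with sparse categories, which the merging rule covers. The sample size and the main comparison need no change.
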